**Fig. 1 Fig1:**
[figure not shown]
Study Flow Chart

**Table 1 Tab1:** WISH Study Data Collection and Outcome Measures

Outcome measure	Baseline (T0)	Mid-intervention (T1)	End of intervention (T2)	13-month follow-up (T3)
Demographic information (age, postcode/Eircode)	X			
Total physical activity (accelerometery)	X	X	X	X
Time spent in sedentary behaviour, and low, moderate and vigorous intensity physical activity (accelerometery)	X	X	X	X
Proportion of pupils meeting current physical activity recommendations (accelerometery)	X	X	X	X
BMI z-scores (height and weight)	X		X	X
Waist: hip ratio (waist and hip circumference)	X		X	X
Coping, resilience and cognitive reappraisal (Emotion Regulation Questionnaire for Children) [55]	X		X	X
Sleep quality, duration and efficiency (Pittsburgh Sleep Quality Index) [56]	X		X	X
Social media use, social integration and emotional connection to social media [57, 58]	X		X	X
Body weight and appearance satisfaction [59]	X		X	X
Self-efficacy for physical activity and walking [60]	X		X	X
Health-related quality of life (Kidscreen-10) [61]	X		X	X
Reasons for engaging in physical activity (BREQ-3) [62, 63]	X		X	X
Friendship nominations	X		X	
Process evaluation: focus groups with all pupils (control & intervention)	X			
Process evaluation: focus groups with intervention pupils			X	
Process evaluation: walk leaders - perception of physical activity and fitness [64], physical activity self-efficacy [65], physical activity enjoyment [66] and leadership skills [67]	X		X	
Process evaluation: interviews with walk leaders			X	
Process evaluation: interviews with teachers			X	

*Abbreviations*: *BMI* Body Mass Index

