### Recruitment

#### School recruitment

The study setting will be post-primary schools in the Border Region of Ireland / Northern Ireland. Using school enrolment data [68, 69], schools that meet the following criteria will be invited to participate:
Northern Ireland: Schools that have at least 80 girls across years 9–10 and located in Co. Derry/LondonderryIreland: Schools in Co. Donegal with an enrolment of > 240 girls

Invitation letters accompanied with an expression of interest form will be sent to school principals. Where requested, a member of the research team will visit the school to provide a short overview of the trial for relevant staff. We aim to recruit 18 schools, of which 9 will be randomly allocated to intervention arm with the other 9 allocated to the control arm. Within each school, at least 24 children will be recruited (i.e., minimum of 432 children in total). Should it not be possible to recruit eighteen schools in the selected counties, schools that meet the inclusion criteria (Northern Ireland: at least 80 girls across years 9–10; Ireland: enrolment of > 240 girls) from other counties across the Border Region of Ireland / Northern Ireland will be invited to participate.

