### Sample size calculations

Sample size calculations are based on the WISH feasibility trial [50], which detected a mean difference of 11.41 min in total physical activity (light, moderate and vigorous intensity physical activity) measured using accelerometery between the intervention (2 schools consisting of a total of 79 children) and control (4 schools consisting of 84 children in total) groups. In order to detect a difference of 11.41 min total physical activity per day between groups, assuming a standard deviation (SD) (pooled intervention and control group SD) of 25 min in total physical activity, a power of 80%, a significance of 0.05, an average cluster size of 20 children, an intra-class correlation of 0.03 (calculated from pilot data [50]), and a coefficient of variation of 0.46, the sample size needed is 15 schools increasing to 16 schools (8 per study arm) to allow for 10% cluster attrition. To allow for 20% loss to follow up we will recruit at least 24 children per cluster (at least 384 children in total). Based on recruitment rates of 34% in our feasibility study [50], all schools that have at least 80 girls across years 9–10 (Northern Ireland) or total enrolment of > 240 girls (Ireland) will be eligible to participate in the study. From the Northern Ireland School Census [68] we estimate that 77 schools meet these criteria and based on 2016 school recruitment data for Ireland [69] 54 post-primary schools meet these criteria.

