#### Quantitative analysis

Outcome data will be reported in accordance with Consolidated Standards of Reporting Trials (CONSORT) guidelines [78]. The statistician performing the data analyses ([name]) will be blinded to allocation throughout the study and statistical analysis will only be undertaken when all data has been collected (T3). Pupils will be included in the analysis regardless of compliance with the physical activity intervention. We will apply a multilevel statistical model using ML- win [79] to assess changes in total physical activity (mins per week) from baseline to post-intervention. Multilevel modelling will also be used for the change in total physical activity at other timepoints and secondary continuous outcomes adjusting the false discovery rate using the Benjamini-Hochberg Procedure [80]. Outcomes will be compared between the control and intervention groups using a 2-level multilevel model, with pupils nested within schools. The models will be adjusted for the child-level covariates (level 1): baseline total physical activity (minutes per week), age and BMI z-score; and the following school-level covariates (level 2): social economic status (postcode/Eircode). In the interests of parsimony, covariates will only be retained if their inclusion results in a significant improvement in fit statistics.

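### Deprivation is measured per pupil but specified as a school-level covariate that must pass a significance test: a small precision loss and a data-driven model, cheaply avoided

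*Protocol article*

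**What the plan says.** Three parts of the protocol article bear on this.

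- **Collection.** Table 1 has a baseline-only row, "Demographic information (age, postcode/Eircode"), so postcode sits beside age as pupil information. The baseline list that closes the Secondary outcomes section says that the home postcode or Eircode is taken to derive the Index of Multiple Deprivation (IMD).
- **Model.** Quantitative analysis specifies a "2-level multilevel model, with pupils nested within schools". Baseline activity, age and BMI z-score are level-1 covariates. Deprivation is listed separately, under "the following school-level covariates (level 2): social economic status (postcode/Eircode").
- **Retention.** The same section then says that "covariates will only be retained if their inclusion results in a significant improvement in fit statistics". This applies to covariates at both levels. Neither the test nor its threshold is given.

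The article does not say how pupil scores would become a school score, and it describes no measure based on the school's own address.

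**The concern.** Age and postcode come from the same row of Table 1, but the model puts one at pupil level and the other at school level. A home-area score varies among pupils of the same school, so the stated level does not match the variable collected. The article fixes both the level and the retention rule, so this is more than detail left to a fuller document.

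The text can be read in three ways:

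1. School mean (or similar): within-school variation in deprivation is discarded.
2. Pupil's own score: the covariate is a level-1 term with the wrong label.
3. The school's own postcode: this is not the variable described under data collection.

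Under the first or third reading the retention rule tests a term that has only 18 distinct values. Such a test has little power, so a real but moderate deprivation gradient could fail it. What is at stake is some precision, and a primary model whose covariates are settled only after the outcome data have been seen.

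**Working it through.** **Inputs from the protocol article**

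- Schools: "We aim to recruit 18 schools, of which 9 will be randomly allocated to intervention arm" and 9 to control, so J = 18 (School recruitment).
- Sample size calculations: "a power of 80%, a significance of 0.05, an average cluster size of 20 children"; difference 11.41 min, SD 25 min, intra-class correlation (ICC) 0.03, coefficient of variation of cluster size 0.46.

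**Assumptions (not in the article)**

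- Two-sided 0.05 for the sample size, and 0.05 for the retention test.
- Equal schools of m = 20 in the retention and precision calculations.
- The ICC of 0.03 applies to the analysed outcome.
- R², the share of between-school variance explained by a school-level deprivation score, is varied from 0 to 1.
- The pupil-level partial correlation of deprivation with the outcome is 0.1 to 0.3.

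**Step 1: reproduce the plan's own figure**

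The article gives no figure for covariate retention. The nearest is its 15 schools.

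- Pupils per arm without clustering: 2 × (25 × (1.960 + 0.842) / 11.41)² = 75.4, so 76.
- Design effect: 1 + ((0.46² + 1) × 20 − 1) × 0.03 = 1.697.
- Total schools, with t quantiles on 13 degrees of freedom: 4 × (25 × (2.160 + 0.870) / 11.41)² × 1.697 / 20 = 14.96, so 15.

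The stated 15 is reproduced, so the ICC and cluster size are used below as the plan uses them.

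**Step 2: chance that a school-level term is dropped**

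For a 1-df likelihood-ratio test the non-centrality is

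λ = J × R² × ICC / [(1 − R²) × ICC + (1 − ICC)/m], with (1 − ICC)/m = 0.97/20 = 0.0485.

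- R² = 0.2: λ = 0.108 / 0.0725 = 1.49
- R² = 0.5: λ = 0.270 / 0.0635 = 4.25
- R² = 1: λ = 0.540 / 0.0485 = 11.13

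The last two columns are checks: a t test on 15 df, and a maximum-likelihood simulation with 600 trials per setting.

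| R² (assumed) | Dropped, likelihood ratio | Dropped, t test | Dropped, simulation |
|---|---|---|---|
| 0 | 95% | 95% | 92% |
| 0.2 | 77% | 79% | 77% |
| 0.3 | 67% | 70% | not run |
| 0.5 | 46% | 51% | 51% |
| 1 | 8% | 12% | 20% |

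**Step 3: precision lost if within-school variation is unused**

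The variance of a school mean is proportional to 0.03 + 0.97/20 = 0.0785. A pupil-level partial correlation r removes r² of the pupil component.

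- r = 0.1: 0.03 + 0.99 × 0.0485 = 0.0780; √(0.0780/0.0785) = 0.997, so the standard error falls by 0.3%.
- r = 0.3: 0.03 + 0.91 × 0.0485 = 0.0741; √(0.0741/0.0785) = 0.972, so it falls by 2.8%.

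**Step 4: cost of a school-level term that is kept but explains nothing**

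It uses one of 16 between-school degrees of freedom. The critical t moves from 2.120 to 2.131, about 0.5%.

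**The case against.** The strongest reply is that adjustment at school level is defensible and the rest is wording. Schools are the randomised units, there are few of them, and chance imbalance between them matters. The between-school part is 0.03/0.0785, or 38%, of the variance of a school mean, and a level-2 covariate targets exactly that part. If it explained 20% of it, the variance would fall to 0.8 × 0.03 + 0.0485 = 0.0725 and the standard error by 3.9%, more than the pupil-level gain in Step 3. A single pupil-level slope also forces the within-school and between-school relations to be equal. All of this stands. It supports offering the school mean alongside the pupil score. It does not support leaving the level undefined, or letting a test on 18 values decide.

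Second, the argument from 18 values presumes aggregation, which the text does not spell out. If each pupil's own score is entered, nothing is lost and only the label is wrong. This also stands, which is why the finding is conditional.

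Third, the retention rule is not specific to deprivation; it covers baseline activity, age and BMI z-score too. That is correct, and the fix should cover them.

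A reader might go further and infer that, with 18 schools, deprivation would almost always be dropped. The figures do not support that. A drop rate above 90% occurs only when deprivation is unrelated to school differences, where dropping it costs nothing; at the other extreme the rate is 8% to 20%. A reader might also set the correlation needed for significance among 18 schools (about 0.44 to 0.48) against that needed among some 346 pupils (about 0.11). Those correlations are on different scales, because the same gradient can look very different among school values and among pupils. The gap therefore does not measure lost sensitivity.

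**Conclusion.** The point holds in a limited form. The article collects deprivation per pupil, specifies it at school level without an aggregation rule, and makes its inclusion depend on a significance test. If it is aggregated, a weak or moderate deprivation effect would often be dropped: about 77% of the time when it explains 20% of between-school variance, and about half the time at 50%. Within-school information would go unused whether or not the term is kept. The price is a standard error that pupil-level adjustment could have made about 0.3% to 2.8% smaller, plus a covariate set that depends on the data.

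These sizes rest on the protocol's ICC and cluster size, an assumed 0.05 retention threshold, and assumed values for R² and the partial correlation, none of which the article supplies. Omitting a baseline covariate does not by itself bias a randomised comparison, so a reader should not infer that the treatment estimate would be biased by socioeconomic differences. This is a free improvement and no threat to the trial's conclusion.

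**What to change.** In Quantitative analysis:

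- List deprivation with the level-1 covariates, as each pupil's own IMD score from the home postcode or Eircode.
- Optionally add the school mean of that score at level 2, defined in the text, to capture between-school differences separately.
- State that deprivation is in the model whatever its significance, and apply the same to baseline activity, age and BMI z-score, so that the full covariate set is fixed before outcome data are analysed.

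The cost is a line or two of text. No new data are needed, because the postcode is already collected for every pupil at baseline. A pupil-level term costs almost nothing in degrees of freedom; the optional school mean costs one between-school degree of freedom, the 0.5% change in critical t shown above.

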#### Qualitative analysis

Semi-structured interviews and focus groups will be audio-recorded, transcribed verbatim and anonymised before being coded. Thematic analysis techniques will be used to generate initial codes using NVivo [version 12] and these will be grouped to form themes for each cohort.

### Participant remuneration

All participating schools will be eligible to claim reimbursement for the use of their facilities and for teacher time (up to a maximum total of €400) and provided with a summary of project findings. At each time point, pupils will be provided with an incentive (earphones; water bottle; charger pack or sports top) when they have returned the accelerometer having worn it for a minimum of 2 days (€17 total cost). Pupils in the intervention group who take part in ten walks will be able to exchange their reward card for a small value incentive (<€1), for example, pen, pencil, ruler.

### Patient and public involvement

The views of low-active adolescents were instrumental in designing the WISH intervention [37, 50, 81]. In advance of the feasibility/pilot, 64 low-active adolescents were consulted on how best to encourage them to increase daily physical activity [37]. The findings informed the development of the school-based, peer-led walking intervention [50]. Following feasibility/pilot, 45 participants provided feedback on both intervention and research components [81]. On the basis of the pilot study, post-primary schools in Northern Ireland (*n* = 208) were surveyed to assess acceptability of a school-based walking intervention [81]. For the current study, Youth Advisory Group (YAG) meetings will be held on four occasions throughout the course of the study (Phase 1: June 2019; Phase 2: March 2020; Post-intervention: June 2021; End of Study: February 2022). Schools from both jurisdictions will be asked to invite pupils aged 12–14 years (participants) and 15–18 years (walk leaders) to the meetings. The YAG will be consulted on all aspects of the research, inform the delivery of the intervention and provide researchers with an understanding of what would encourage/discourage participation. The YAG will advise on resources for pupils and be actively engaged in the dissemination of the findings. In addition, the walk leader training has been developed in consultation with the Physical Activity Co-ordinator (Western Health and Social Care Trust).

### Dissemination of project findings

In order to disseminate the findings of the study we will hold two dissemination events, one in Northern Ireland and one in Ireland. These will be open to all stakeholders and will present the findings of the research and provide further information on how schools could implement the programme. In addition, all materials used in the intervention will be made available to control schools and to both Education Authorities for dissemination to all schools in the Border Region of Northern Ireland / Ireland. Peer-reviewed publications will allow the results to be disseminated to the scientific community and policy makers. All papers will be submitted for publication in open access journals.

## Discussion

To our knowledge, this is the first fully powered trial that will investigate the effectiveness of a peer-led brisk walking intervention in adolescent girls. The current study builds on a promising pilot trial [50] which confirmed the feasibility of our planned intervention. Patient and public engagement has been and will continue to be central to this study which enhances the acceptability of the intervention, ensures that research is relevant and increases the self-esteem of those staff involved in the project [82].

The WISH Study aims to address several gaps in the current scientific evidence for walking interventions in adolescents. Firstly, until now there have been a limited number of studies which investigate the longer-term effectiveness of physical activity interventions, particularly in children and adolescents [31]. The current study includes longer-term follow up and will measure physical activity at 13 months’ post-intervention to address the paucity of evidence on the longer-term effectiveness of physical activity interventions in children and adolescents. Secondly, the WISH Study aims to provide adolescent girls with extra opportunities to be active at break and lunchtime and given the limited number of structured walking recess-based interventions [31], this study will address this specific gap in the current evidence base. In terms of study methodology, it is estimated that there are more than twelve methods available for measuring physical activity [83] and although there is no universally agreed “gold standard” method [84–86] the use of accelerometers enables us to objectively measure physical activity and provide information on the intensity, duration and frequency of physical activity [85, 87].

In accordance with MRC guidelines [88], the research team will undertake an in-depth mixed method process evaluation and the perspectives of multiple stakeholders (i.e. pupils, walk leaders and teachers) will be sought. This will enable a robust evaluation of how the intervention was implemented and an accurate interpretation of either positive and/or negative outcomes [89, 90].

To conclude, if the WISH intervention increases physical activity, there is potential for the programme to be widely implemented by schools resulting in a sustainable, long-term, positive impact on adolescent population health.

## Data Availability

Not applicable at this point.

## Abbreviations

CONSORT: Consolidated Standards of Reporting Trials
c-RCT: Clustered Randomised Controlled Trial
BMI: Body Mass Index
IMD: Index of Multiple Deprivation
MRC: Medical Research Council
MVPA: Moderate-to-vigorous physical activity
NICHE: Nutrition Innovation Centre for Food and Health
PE: Physical Education
SD: Standard Deviation
SDT: Self-Determination Theory
WISH: Walking In ScHools
YAG: Youth Advisory Group
